# Fibrinogen Early In Severe Trauma studY (FEISTY): study protocol for a randomised controlled trial

**DOI:** 10.1186/s13063-017-1980-x

**Published:** 2017-05-26

**Keywords:** Fibrinogen, Trauma, Haemorrhage, Cryoprecipitate, Fibrinogen concentrate, ROTEM®

## Abstract

**Background:**

Haemorrhage is a leading cause of death in severe trauma. Fibrinogen plays a critical role in maintaining haemostasis in traumatic haemorrhage. Early fibrinogen replacement is recommended by several international trauma guidelines using either fibrinogen concentrate (FC) or cryoprecipitate (Cryo). There is limited evidence to support one product over the other with widespread geographic and institutional variation in practice. This pilot trial is the first randomised controlled trial comparing FC to Cryo in traumatic haemorrhage.

**Methods/design:**

The Fibrinogen Early In Severe Trauma studY (FEISTY) is an exploratory, multicentre, randomised controlled trial comparing FC to Cryo for fibrinogen supplementation in traumatic haemorrhage. This trial will utilise thromboelastometry (ROTEM®) to guide and dose fibrinogen supplementation. The trial will recruit 100 trauma patients at four major trauma centres in Australia. Adult trauma patients with evidence of haemorrhage will be enrolled on arrival in the trauma unit and randomised to receiving fibrinogen supplementation with either FC or Cryo. The primary outcome is the differential time to fibrinogen supplementation. There are a number of predetermined secondary outcomes including: effects of the intervention on plasma fibrinogen levels, feasibility assessments and clinical outcomes including transfusion requirements and mortality.

**Discussion:**

The optimal method for replacing fibrinogen in traumatic haemorrhage is fiercely debated. In this trial the feasibility and efficacy of fibrinogen supplementation using FC will be compared to Cryo. The results of this pilot study will facilitate the design of a larger trial with sufficient power to address patient-centred outcomes.

**Trial registration:**

ClinicalTrials.gov, ID: NCT02745041. Registered 4 May 2016.

**Electronic supplementary material:**

The online version of this article (doi:10.1186/s13063-017-1980-x) contains supplementary material, which is available to authorized users.

## Background

Despite advances in trauma management over the last decade, haemorrhage in the setting of severe trauma remains a leading cause of morbidity and mortality [1, 2]. Death related to major haemorrhage is potentially preventable and represents a target for mortality reduction strategies. Traumatic haemorrhage is complicated by a complex coagulopathy – trauma-induced coagulopathy (TIC); the pathophysiological mechanisms of which are incompletely understood [3, 4].

Fibrinogen plays a critical role in maintaining effective haemostasis in traumatic haemorrhage and TIC [5, 6]. Fibrinogen is important in both primary haemostasis through platelet aggregation and secondary haemostasis where it is cleaved by thrombin to form fibrin [7, 8]. Fibrinogen is a glycoprotein synthesised in the liver and the healthy adult has a plasma fibrinogen concentration of between 2 to 4 g/L. Hypofibrinogenaemia and increased fibrinogen breakdown are key elements of TIC and fibrinogen is usually the first factor to reach critically low levels in traumatic haemorrhage [9, 10]. Hypofibrinogenaemia after severe trauma is associated with an increased risk of massive transfusion and death [11–13]. It is postulated that early fibrinogen replacement may assist in haemorrhage control, improve coagulopathy and reduce transfusion requirements [13–15]. Recently published trauma guidelines suggest that fibrinogen supplementation should occur in the presence of plasma fibrinogen levels <1.5–2 g/L or thromboelastometric signs of fibrinogen deficiency [16].

Major haemorrhage protocols (MHP) are a key component of the damage control approach to the severely bleeding trauma patient and the successful implementation of a MHP does improve outcomes [17, 18]. However, the ideal trauma MHP remains elusive, with considerable geographical and institutional variation [19, 20]. The three most commonly utilised MHP are: (1) high fixed-ratio blood product to packed red blood cell transfusion (PRBC) transfusion, (2) targeted blood product transfusion in response to viscoelastic haemostatic assay (VHA) results and (3) a hybrid approach utilising a high fixed ratio initially and subsequently transitioning to a VHA-guided approach [21, 22].

Regardless of which approach is used fibrinogen can be replaced with plasma, cryoprecipitate (Cryo) and fibrinogen concentrate (FC) each containing different amounts of fibrinogen; 2 g/L, 8–16 g/L and 20 g/L, respectively. The low concentration of fibrinogen in plasma and the large volumes required potentially make it unsuitable for dedicated fibrinogen supplementation [23–25]. The RETIC trial (NCT01545635) comparing plasma to factor concentrate-based resuscitation has recently been terminated early after an interim analysis revealed potential harm to patients randomised to the plasma arm. Cryoprecipitate contains substantially higher concentrations of fibrinogen than plasma and is widely accepted as the standard of care for fibrinogen supplementation in severe haemorrhage [26]. However, its use is not currently supported by high-level evidence [27]. The CRYOSTAT trial reported in 2015 that early fibrinogen supplementation utilising Cryo was feasible and effectively maintained fibrinogen levels in traumatic haemorrhage [28]. The use of FC has a number of theoretical advantages including: standard dose per vial, reduced volume, viral inactivation, no requirement for ABO compatibility matching, ease of reconstitution and administration. However, in severe trauma there are no robust clinical trials to demonstrate a survival or cost-effectiveness benefit compared to Cryo [6, 25, 29].

A number of key questions regarding fibrinogen supplementation in traumatic haemorrhage remain unanswered, including: (1) What tests, if any should be utilised to guide fibrinogen therapy? (2) What is the optimal product for fibrinogen replacement? (3) What is the optimal dose of fibrinogen? and (4) What is the impact of early fibrinogen replacement on clinically important outcomes?

The objectives of this trial are to assess the feasibility of early fibrinogen replacement utilising FC compared to the use of Cryo in patients with traumatic haemorrhage and viscoelastic evidence of hypofibrinogenaemia. We hypothesise that fibrinogen replacement to reverse hypofibrinogenaemia in traumatic haemorrhage may be achieved more rapidly, and with a more predictable dose response, using FC compared to Cryo.

## Methods/design

This is an investigator-initiated, pilot, multicentre, randomised controlled trial (RCT) comparing FC to Cryo for fibrinogen replacement in traumatic haemorrhage. The trial will take place in four major trauma centres in Queensland, Australia. The protocol adheres to the Standard Protocol Items: Recommendations for Interventional Trials (SPIRIT) Statement (Additional file 1).

### Patients

The trial will enrol 100 adult (aged 18 years or older) trauma patients judged by treating clinicians to have clinically significant haemorrhage or potential for significant transfusion requirements with an Assessment of Blood Consumption Score (ABC Score) ≥2. The ABC Score is a well-validated tool for the prediction of massive transfusion, has been utilised in a recent civilian trauma haemorrhage RCT and is simple to apply in the complex multidisciplinary environment of major trauma resuscitation [30–32]. See Table 1 for full inclusion and exclusion criteria.

**Table 1 Tab1:** Inclusion and exclusion criteria

Inclusion criteria:	
Adult (≥18 years) affected by trauma *and*	
Judged to have significant haemorrhage *or*	
Predicted to require significant transfusion with ABC Score ≥2	
or by treating clinician judgment	
Exclusion criteria:	
Injury judged incompatible with survival	
Previous fibrinogen administration this admission	
Pretrauma centre dedicated fibrinogen replacement	
Known objection to blood products	
Known coagulation disorder	
Pregnancy	
Enrolment in competing study	

### Randomisation

A computer-generated 1:1 block randomisation schedule has been produced by a statistician independent to the study, accommodating unequal recruitment across the four initial sites together with the possibility of additional trial sites. Secure, password-protected web-based randomisation will occur on patient arrival to a participating hospital trauma unit once inclusion and exclusion criteria have been assessed. Each patient will receive fibrinogen supplementation comprising either protocol-directed FC or Cryo therapy. Allocation concealment will be maintained through to the conclusion of the web randomisation process, but for practical and safety reasons, randomised trial patients and their treating health care professionals will not be blind to the trial intervention. Trial integrity will be supported by maintenance of blinding for outcome assessors and the trial statistician.

### Intervention

After compliance with consent requirements and with the treating clinician’s approval, patients will be randomised to receive fibrinogen supplementation using either FC (Riastap®, CSL Behring GmbH, Marburg, Germany) or Cryo (Australian Red Cross Blood Service). The requirement for fibrinogen supplementation will be defined by a FIBTEM A5 (clot amplitude 5 min after clot formation) ≤10 mm together with a clinical scenario suggesting significant haemorrhage. The intervention will be performed in randomised patients as soon as possible after each FIBTEM threshold result becomes known. Patients will remain in their allocated intervention arm for the duration of their hospital admission up to 30 days. Dosing of FC and Cryo will be guided by the FIBTEM A5 result as per trial protocol (Fig. 1). FC will be administered by intravenous injection and Cryo by rapid intravenous infusion. Fibrinogen supplementation will be continued throughout the resuscitation according to protocol and as per the allocated intervention arm (Fig. 1).

**Fig. 1 Fig1:**
[figure not shown]
Intervention and dosing strategy

All other care received by trial patients will be prescribed by the managing staff according to relevant local hospital clinical and trauma guidelines that are based on Emergency Management of Severe Trauma (EMST) or Advanced Trauma Life Support (ATLS) principles. In all centres a Damage Control Resuscitation (DCR) approach to the management of severe trauma is standard practice; with rapid identification and treatment of life-threatening injuries, organ support and subsequent definitive injury management once the patient has been stabilised [33]. In patients with suspected haemorrhage the focus is geared towards rapid identification and surgical or interventional radiological control of haemorrhage. In all centres focused bedside ultrasound scan (USS) and whole body ‘Trauma’ computed tomography (CT) imaging when haemodynamic stability permits is standard of care. All centres have a ‘Red Blanket’ protocol with rapid transfer directly to the operating room (OR) for the haemodynamically unstable and exsanguinating trauma patient. Concurrent with haemorrhage control – haemostatic resuscitation (HR) is employed, involving blood product transfusion, correction of acidaemia, temperature control and organ support in an attempt to maintain ‘normal’ physiology.

### Trial endpoints

The primary outcome is the time interval in minutes from FIBTEM analysis and clinical scenario suggesting that fibrinogen supplementation is required to the completion of the first administration of fibrinogen supplementation (FC or Cryo). It is aimed to administer the FC intervention within 30 min of fibrinogen requirement being identified. Consistent with the exploratory pilot nature of this study, multiple hypothesis-generating outcomes will be evaluated together with assessments of process feasibility, including:Effects of fibrinogen supplementation (FC and Cryo) on plasma fibrinogenTime to randomisationTime course of fibrinogen levels as measured by FIBTEM and Clauss Fibrinogen (FibC)Transfusion requirementsClinically relevant thromboembolic complicationsMortality at several time points including hospital discharge and 90 days

Detailed data collection will occur for the first 7 days of hospital admission and extended follow-up to 90 days (see the SPIRIT figure in Fig. 2). See Table 2 for full primary, secondary and feasibility outcomes.

**Fig. 2 Fig2:**
[figure not shown]
Fibrinogen Early In Severe Trauma studY (FEISTY) Standard Protocol Items: Recommendations for Interventional Trials (SPIRIT) flowchart

**Table 2 Tab2:** Outcome measures

Primary outcome measures:	
1. (A) Time to administration of fibrinogen administration (FC or Cryo) from time of ROTEM® analysis and clinical scenario suggesting that fibrinogen supplementation is required	
1. (B) Feasibility of administering FC within 30 min of ROTEM® and clinical scenario suggesting that fibrinogen supplementation is required	
2. Effects of fibrinogen supplementation (FC and Cryo) on fibrinogen levels as measured by FIBTEM and Clauss Fibrinogen (FibC)	
Secondary outcome measures:	
1. Transfusion requirements (in number of units) of PRBC, FFP, FC, Cryo, platelets, PCC at 4, 6, 12, 24 and 48 h	
2. Duration of bleeding episode or time until surgical haemorrhage control with no further coagulation factors	
3. Duration of mechanical ventilation	
4. Duration of ICU and hospital LOS	
5. ROTEM® (Sigma and Delta), Multiplate®, FBC, INR, APTT, FibC analysis at prespecified time points	
6. Evaluation of EXTEM CT in response to fibrinogen supplementation	
7. Adverse events: TACO, TRALI, Sepsis, MOF	
8. Thromboembolic complications	
9. All-cause mortality at 4, 6, 24 h and up to 90 days	
Feasibility outcome measures:	
1. Transfusion requirements (in number of units) of PRBC, FFP, FC, Cryo, Platelets, PCC at 4, 6, 12, 24 and 48 h	
2. Duration of bleeding episode or time until surgical haemorrhage control with no further coagulation factors	
3. Duration of mechanical ventilation	
4. Duration of ICU and hospital LOS	
5. ROTEM® (Sigma and Delta), Multiplate®, FBC, INR, APTT, FibC analysis at prespecified time points	
6. Evaluation of EXTEM CT in response to fibrinogen supplementation	
7. Adverse events: TACO, TRALI, Sepsis, MOF	
8. Thromboembolic complications	
9. All cause mortality at 4, 6, 24 h and up to 90 days	
Feasibility outcome measures:	
1. Time to randomisation	
2. FC and Cryo wastage	
3. Proportion of patients with blood sampling at all prespecified time points	
4. Number of missed patients (eligible but not enrolled)	
5. Randomisation errors	
6. Protocol violations	

*APTT* Activated Partial Thromboplastin Time, *Cryo* cryoprecipitate *EXTEM CT* clotting time, FBC full blood count, *FC* fibrinogen concentrate, *FFP* fresh frozen plasma, *FibC* Clauss Fibrinogen, *ICU* intensive care unit, *INR* International Normalised ratio, *LOS* length of stay*, MOF* Multiple organ failure, *PCC* Prothrombin complex concentrate, PRBC packed red blood cells, *ROTEM*® thromboelastometry, *TACO* transfusion-associated circulatory overload, *TRALI* transfusion-related acute lung injury

### Blood sampling

As previously stated the requirement for fibrinogen supplementation will be guided by FIBTEM A5 (ROTEM® Sigma) analysis. A number of other blood tests to assess haemostasis will be performed at predefined time points from admission to day 7 (Fig. 2). These include: ROTEM® Sigma and Delta (FIBTEM, EXTEM, INTEM, HEPTEM), Multiplate® (ADP, ASP, TRAP), TEG 6S (CK, CKH, CRT, CFF), haemoglobin, platelet count, International Normalised Ratio (INR), Activated Partial Thromboplastin Time (APTT), Clauss Fibrinogen. Arterial blood gas analysis (pH, lactate, base deficit, HCO_3_
^−^) will be performed on admission and as clinically indicated. Likewise, blood chemistry results assessing organ function will be performed at the discretion of the treating clinical staff.

### Sample size

The total pilot trial sample size of 100 patients (allocated 1:1 to FC or Cryo) was set based on estimated recruitment rates across four sites and on available budget. An anticipated 70% of participants will be male, consistent with the usually observed sex ratio in severe trauma patients. Using local data combined with the published interquartile range of time intervals in a recent trial of early Cryo administration for major traumatic haemorrhage, an approximate standard deviation (SD) was derived of 14 min for each treatment arm primary outcome. Assuming this SD and normally distributed time intervals, a trial with 100 evaluable patients, equally divided between two groups, would have approximately 80% power to detect a difference of ± 8 min between mean FC and Cryo treatment intervals, at a type 1 (alpha) error of 5%. With a fixed (*n* = 100) total sample size, the SD of time intervals actually observed will have a marked influence on trial power, as summarised in Fig. 3. For example, an increase in each group SD from 14 min to 30 min would increase the detectable difference between mean responses of experimental and control subjects from 8 min to 17 min. Additionally, 100 patients recruited across four sites will enable accurate assessment of the feasibility outcome measures which are an important component of this pilot trial.

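### Power and detectable difference are stated as if all 100 randomised patients had a primary outcome, but only those who later meet the FIBTEM trigger can have one

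*Protocol article*

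**What the plan says.** The Sample size section opens with "The total pilot trial sample size of 100 patients (allocated 1:1 to FC or Cryo") and says that this number came from expected recruitment and the available budget. It then reports that "an approximate standard deviation (SD) was derived of 14 min for each treatment arm primary outcome" and, on that basis, that "a trial with 100 evaluable patients, equally divided between two groups, would have approximately 80% power to detect a difference"; the target is 8 min in either direction, with alpha at 5%. The next sentences call the total of 100 fixed and vary only the SD: raising it from 14 to 30 min moves the detectable difference from 8 to 17 min (Fig. 3).

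Four other places decide who can have a primary outcome:

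- **Patients, Table 1:** entry is by judged haemorrhage, an ABC Score of 2 or more, or clinician judgement. No FIBTEM result is required.
- **Randomisation:** "web-based randomisation will occur on patient arrival to a participating hospital trauma unit once inclusion and exclusion criteria have been assessed".
- **Intervention:** "The requirement for fibrinogen supplementation will be defined by a FIBTEM A5" of 10 mm or less, together with a clinical scenario suggesting significant haemorrhage.
- **Trial endpoints:** the primary interval starts when FIBTEM and the clinical scenario indicate a need, and ends when the first administration is complete.

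Two statements point the other way. The Randomisation section says that each patient will receive fibrinogen supplementation. The objectives, at the end of the Background, describe patients with viscoelastic evidence of hypofibrinogenaemia.

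**The concern.** A randomised patient who never meets the trigger has no start time, no administration and so no primary interval. Whether a patient is evaluable depends on a result obtained as part of care after entry, not on eligibility. Yet the Sample size section uses 100 both as the fixed number randomised and as the number evaluable, and its sensitivity analysis leaves the evaluable number untouched.

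This affects how the result will be read. If a material share of patients do not trigger, a null comparison would be judged against about 80% power for 8 min that the trial does not have. The larger trial that this pilot is meant to inform could also inherit the assumption that everyone randomised contributes to a time-to-treatment endpoint.

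The same denominator governs primary outcome 1(B) in Table 2, FC given within 30 min. It can be estimated only in FC patients who reach the trigger, who may be fewer than 50.

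**Working it through.** **Inputs.** From the Sample size section: 100 patients, 1:1, so n = 50 per arm; SD 14 min (alternative 30 min); difference 8 min; alpha 5%. From the interim analysis section: two-sided testing. The proportion reaching the trigger is not given, so it is varied below as an assumption.

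**Step 1: reproduce the stated figures.** The standard error of the difference in means is SD × √(2/n) = 14 × √(2/50) = 2.80 min.

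- Power, normal approximation: Φ(8/2.80 − 1.96) = Φ(0.897) = 81.5%. With the noncentral t distribution (98 df) it is 80.8%.
- Detectable difference at 80% power: (1.96 + 0.84) × 2.80 = 7.8 min, or 7.9 min with the t distribution.
- At SD 30: (1.96 + 0.84) × 30 × √(2/50) = 16.8 min, or 17.0 min with the t distribution.

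The stated 80%, 8 min and 17 min are all reproduced for 50 evaluable patients per arm.

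**Step 2: how much slack is there?** The normal approximation needs 49 per arm for 80%. At 49 per arm the t calculation gives 80.0%; at 48 per arm it gives 79.1%. So the figure holds with at most about two of the 100 patients not evaluable.

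**Step 3: vary the evaluable fraction f.** Put n = 50f per arm, assuming equal fractions in the two arms, and repeat the t calculation.

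| Evaluable fraction (assumed) | n per arm | Power for 8 min, SD 14 | Detectable difference, SD 14 | Detectable difference, SD 30 |
|---|---|---|---|---|
| 100% | 50 | 80.8% | 7.9 min | 17.0 min |
| 90% | 45 | 76.5% | 8.4 min | 17.9 min |
| 80% | 40 | 71.4% | 8.9 min | 19.0 min |
| 60% | 30 | 58.6% | 10.3 min | 22.1 min |
| 50% | 25 | 50.8% | 11.3 min | 24.3 min |

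The normal approximation gives slightly higher power (77.4%, 72.4%, 60.0% and 52.4% for the last four rows).

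**Step 4: precision of outcome 1(B).** Exact (Clopper-Pearson) 95% intervals: 25 of 50 treated FC patients gives 36% to 64%; 12 of 25 (48%) gives 28% to 69%.

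**The case against.** **The sentence is conditional and true.** It speaks of evaluable patients, and for 100 of them the power is as stated. This stands: a reader might call it an arithmetic error, and it is not. But the conditional wording does not settle the matter, because the 17 min example is tied to the fixed total of 100 and no allowance separates the randomised from the evaluable.

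**The article says each patient will be treated.** If so, all 100 would be evaluable. That premise conflicts with Table 1 and the Intervention section, under which a patient can be randomised and never qualify. Fig. 1 is not available here. Treatment may follow any threshold result during resuscitation, so a patient above the threshold on arrival can still trigger later. This raises the evaluable fraction but does not make it 100%.

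**Intention-to-treat keeps everyone.** The Statistical analysis section includes all randomised patients, but that cannot supply a start time for someone who never triggered.

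**Deaths and withdrawals.** A reader might add these as further full losses. The text does not support that: a triggered patient who dies before administration is complete can be censored in the Kaplan-Meier and Cox analyses, and only patients who withdraw consent for use of all data are excluded.

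**The feasibility claim.** A reader might also infer that the promise of accurate feasibility assessment fails. In the last list of Table 2 those measures are time to randomisation, wastage, sampling completeness, missed patients, randomisation errors and protocol violations. Most do not need the trigger. FC within 30 min is listed as a primary outcome, so only its own precision is affected.

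**It is a pilot sized by budget.** This stands and lowers the severity. The article nevertheless publishes a power and a detectable difference, and these should describe the design.

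**Conclusion.** The point holds, with moderate severity. The calculation is correct, but its input is the number randomised where it should be the number who reach the trigger. If more than about two patients do not trigger, power is overstated and the detectable difference understated.

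The direction follows from the article's own rules. The size does not: no trigger rate is given, and nothing in the text favours 50% over 90%. Across that assumed range, power for 8 min runs from about 51% to 76–77%. The detectable difference runs from 11.3 down to 8.4 min at SD 14, and from 24.3 down to 17.9 min at SD 30. A reader might conclude that the trial has only about half the chance of detecting 8 min; that is one end of an assumed range, not a finding.

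The figures also rest on the article's own simplifications: normally distributed intervals, a common SD and a comparison of means, whereas the planned primary analysis is a Cox model.

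**What to change.** 1. Keep 100 randomised patients. In the Sample size section and Fig. 3, restate power and detectable difference for the number expected to reach the trigger, or show them as a function of the evaluable fraction beside the SD.
2. Base the expected fraction on the trigger rate pooled across arms, if it can be obtained. The Trial status section reports 40 patients enrolled but gives no trigger data, so this needs checking. A pooled rate does not reveal results by arm.
3. Give the precision of primary outcome 1(B) for treated FC patients only.
4. Reconcile the statement in Randomisation that every patient receives fibrinogen, and the description of patients in the objectives, with Table 1 and the Intervention section.

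The cost is the rewording of a few sentences and one figure, and a less favourable stated power. No extra patients are needed.

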### Statistical analysis

Data analyses will be performed with a coded binary treatment indicator to preserve blinding to treatment allocation until the trial report is finalised by the writing committee. The trial primary and main secondary outcomes will be reported using intention-to-treat analyses based on all randomly assigned patients, except any who withdraw consent for use of all trial data.

Baseline variables will be summarised using descriptive statistics. The trial primary outcome and other time-to-event outcomes will be displayed as Kaplan-Meier curves and compared between treatments with Cox proportional hazards regression including, as covariates, the trial site stratification factor and patient age and sex. Sensitivity analyses will be performed using unadjusted Cox models which include a binary indicator of treatment as the only covariate, and also using multivariable Cox models including any other baseline covariates exhibiting substantial imbalance between randomisation arms. Lack of proportionality in any Cox model on testing will result in that outcome being assessed using a log-rank test and summarised using the Kaplan-Meier estimated median time to event [34]. Other secondary analyses, including assessment of the differential proportion of thromboembolic complications and mortality at specified time points, will be compared using either chi-square or Fisher exact tests, and also using logistic regression adjusting for the same covariates used in the Cox models. Results will be summarised using frequency tables, and risk ratios or odds ratios as appropriate, with 95% confidence intervals. Approximately normally distributed continuous variables (either untransformed or following log or other normalising transformation) will be compared using *t* tests, or otherwise compared using nonparametric methods (Mann-Whitney).

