### Data and Safety Monitoring Committee and interim safety analysis

An independent Data and Safety Monitoring Committee (DSMC) will conduct two equally spaced interim analyses, at one third (*n* = 33) and two thirds (*n* = 67) of the time into trial recruitment, to assess the differential proportions of all-cause hospital mortality (censored at 30 days for practical reasons) observed in intervention (FC) compared with control (Cryo) patients.

These interim analyses will follow a group sequential plan (Fig. 4) employing symmetrical, two-sided, Haybittle-Peto, three-standard deviation thresholds to evaluate a standardised test statistic (|*Z*
_*k*_| ≥ 3) calculated from a normal approximation to the discrete binomial difference observed between treatment and control groups in mortality. Assuming no early stopping, *k* = 3 planned analyses will occur, with all-cause mortality assessed at *n* = 33, 67 and 100 patients (Fig. 4). Accounting for the type I error spent in these two interim mortality analyses, and in the absence of early stopping, a precise analysis of the trial primary outcome at full recruitment could be conducted at *p* < 0.048 (|*Z*
_*3*_| > 1.975) rather than the conventional statistical significance level (*p* < 0.05; |*Z*
_*1*_| > 1.96). However, in accord with common practice with a small number of interim analyses and symmetrical two-sided, three-standard deviation, Haybittle-Peto thresholds, this trial’s primary analysis will ignore the very small error spent conducting two interim analyses, and evaluate the final primary trial outcome at the conventional two-sided level of 0.05. The DSMC may conduct additional interim analyses of mortality or other outcomes at the committee’s discretion with adjustment to the final level of significance (*p* value) if required.

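### The stated 80% power is for a comparison of mean minutes; the planned unadjusted Cox or log-rank comparison has about 73–74% under the same assumptions, and no mean difference with a confidence interval is named

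*Protocol article*

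**What the plan says.** The Sample size section fixes the total first: "The total pilot trial sample size of 100 patients (allocated 1:1 to FC or Cryo) was set based on estimated recruitment rates" and on budget. It then works out what that number can detect. On spread, "an approximate standard deviation (SD) was derived of 14 min for each treatment arm primary outcome". On power, it takes normal times and 50 evaluable patients in each arm and gives about 80% for a gap of 8 min "between mean FC and Cryo treatment intervals, at a type 1 (alpha) error of 5" per cent. It adds that an SD of 30 min would move the detectable difference from 8 to 17 min. No hazard ratio or event count appears there.

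The Statistical analysis section names a different comparison for the same outcome: "The trial primary outcome and other time-to-event outcomes will be displayed as Kaplan-Meier curves and compared between treatments with Cox proportional hazards regression", adjusted for site, age and sex. Unadjusted Cox models are a sensitivity analysis. If proportionality fails on testing, a log-rank test and Kaplan-Meier medians take over. The t test is named only for continuous variables, after the primary outcome has gone to Cox.

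The section on interim safety analysis says the trial will "evaluate the final primary trial outcome at the conventional two-sided level of 0.05", so the test is two-sided at 5%.

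**The concern.** Power belongs to a test, and the two sections name different tests. The power statement begins "Assuming this SD and normally distributed time intervals" and compares means. Two normal distributions with equal SD and shifted means do not have proportional hazards, so the sizing assumption and the Cox model assumption cannot both hold exactly. For a normal shift the log-rank and Cox tests are also less efficient than the t test, so the quoted power would be too high for them.

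The second issue is scale. The detectable difference is in mean minutes, while the Cox model returns a hazard ratio. A reader could not set the primary result directly against the 8 min in the power statement. The article says the pilot's results will be used to design a larger trial, and an estimate in minutes would help with that.

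**Working it through.** **Inputs.** From Sample size: 50 per arm, SD 14 min in each arm, difference 8 min, normal times, 100 evaluable; second scenario SD 30 min and 17 min. From the interim analysis section: two-sided 0.05. From Statistical analysis: Cox model, log-rank fallback.

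**1. Reproduce the stated power (comparison of means).**
- Standard error = SD × √(2/n) = 14 × √(2/50) = 2.8 min.
- Standardised difference = 8 / 2.8 = 2.857.
- Normal approximation: power = Φ(2.857 − 1.960) = Φ(0.897) = 81.5%. The exact noncentral t gives 80.8%.
- Detectable difference at 80% = (1.960 + 0.842) × SD × √(2/50): 7.8 min at SD 14 and 16.8 min at SD 30.

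The article's 80%, 8 min and 17 min all reproduce. There is no arithmetic error.

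**2. Proportional hazards under the same assumptions.** Let z be the time in SD units from the Cryo mean. The hazard is φ(z)/(1 − Φ(z)) for Cryo and the same function at z + 8/14 = z + 0.571 for FC. Their ratio is:

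| z | hazard ratio, FC to Cryo |
|---|---|
| −2 | 2.8 |
| 0 | 1.5 |
| +2 | 1.2 |

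The ratio is not constant. The fallback does not recover power, because the log-rank test is the score test of the unadjusted Cox model.

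**3. Power of the unadjusted Cox and log-rank tests.** Simulation with normal times, SD 14, shift 8 min, 50 per arm, everyone observed, 20,000 trials:

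| Test | Power |
|---|---|
| Cox, Wald | 73.6% |
| Cox, likelihood ratio | 73.5% |
| Log-rank (score) | 74.0% |
| t test, same data | 81.2% |

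The median estimated hazard ratio is about 1.71. As a cross-check, Schoenfeld's formula with 100 events gives 75.6% at a hazard ratio of 1.7 and needs about 1.75 for 80%.

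At SD 30 and 17 min the standardised shift is 17/30 = 0.567, almost the same as 8/14 = 0.571. The log-rank power is about 73%, against 80% for the t test.

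**4. Detectable difference for the log-rank test.** Simulated power is 79.3% at 8.6 min and 81.1% at 8.8 min, so 80% falls at about 8.7 min. Scaled to SD 30: 8.7 × 30/14 ≈ 18.6 min, against the stated 17.

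**5. The adjusted Cox model (the primary analysis).** The article does not say how much of the variance site, age and sex explain. The shares below are assumed (6,000 trials each):

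| Variance explained (assumed) | Power |
|---|---|
| 0% | 73% |
| 5% | 76% |
| 10% | 77% |
| 15% | 80% |
| 20% | 83% |
| 30% | 87% |

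The adjusted Wald test was somewhat liberal in this setting (6.9% under the null with non-prognostic covariates), so these powers are slightly flattering.

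**6. Sensitivity to shape (assumed, not in the article).** With the same SD and 8 min difference, lognormal or gamma times with control means of 30 to 60 min gave about 66–73% for the unadjusted tests. A shape with truly proportional hazards (minimum-Gumbel) gave about 95%.

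**The case against.** The strongest reply is that the gap is small beside uncertainty the article already admits. It calls both the SD and the power approximate and warns that the observed SD will strongly affect power. An SD of 15.3 instead of 14 would by itself take the t test to 73.5%, and moving from 8 to 8.7 min is minor next to the stated range of 8 to 17 min. This stands as a limit on the importance of the point. It does not make the 80% belong to the Cox analysis.

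Three stronger readings are tempting, and the document does not support them.

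- A reader might infer that the primary analysis has 73% power outright. That holds for the adjusted model only if its covariates carry no information. The Discussion lets each centre place the ROTEM device at the bedside or in the laboratory and reports differing experience with such testing, so site may well be prognostic.
- A reader might infer that the trial was sized to a target of 8 min. The total was set by recruitment and budget, and 8 min is what that total could detect. The only stated time goal is FC within 30 min.
- A reader might infer that no result in minutes will ever appear. The fallback reports Kaplan-Meier medians, and under normality a difference in medians equals a difference in means. The narrower statement holds: no mean difference with a confidence interval is named for the primary outcome.

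It is also fair to say that Cox or log-rank is a defensible choice for time to completed treatment, especially if times are skewed or censored. Demoting it would change the estimand, and correcting the power does not require that.

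**Conclusion.** The point holds as a mismatch between design and analysis, not as an arithmetic error. The stated power overstates that of the unadjusted Cox or log-rank comparison by about 6 to 7 points (80% against 73–74%), equivalent to a detectable difference of about 8.7 min instead of 8. This rests on the article's own premises: normal times, equal SD, 50 evaluable per arm and no censoring. For the adjusted primary model the shortfall runs from about 7 points to none as the covariates' share of variance goes from 0 to about 15%, and it reverses beyond that. The difference in scale between the power statement and the hazard ratio needs no simulation. Because this is an exploratory pilot with a fixed total, the consequence is a misattributed power figure and an unnamed estimate in minutes, not a wrongly derived sample size.

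**What to change.** Keep the Cox model as primary if the investigators prefer it, and make two changes in wording.

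1. In Sample size, say that the 80% refers to a comparison of means. Give the power of the unadjusted Cox or log-rank comparison as about 73–74%, or its detectable difference as about 8.7 min, and state the assumptions (normal times, SD 14 min, 100 evaluable, no censoring). If a figure is quoted for the adjusted model, state the variance assumed to be explained by site, age and sex.
2. In Statistical analysis, add a between-arm difference in minutes with a 95% confidence interval, reported beside the hazard ratio whether or not proportionality holds. Use the mean, or the restricted mean if any times are censored.

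The cost is a few sentences, a slightly less favourable power figure and one extra estimate. No patients are added.
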